Based on the clarification provided by [name] (see below), NCCIH is approving the revised protocol (version 6.0) for the parent study and ancillary study (funded by the ORWH supplement). Please keep a copy of this communique for the study's regulatory binder. Once the study has received IRB approval for the revised protocol, then please so inform NCCIH of said approval.

Regards,

[name]

[name], DC, PhD, DABCO  
Deputy Director, Division of Extramural Research  
National Center for Complementary and Integrative Health (NCCIH)  
National Institutes of Health (NIH)  
[name]  
[name]  
Office: [contact]; [contact]  
[contact]  
Web: [nccih.nih.gov](http://nccih.nih.gov)

[figure not shown]

---

**From:** [name] [<mailto:[contact]>]  
**Sent:** Thursday, June 30, 2016 7:41 AM  
**To:** [name] (NIH/NCCIH) [E] <[[contact]](mailto:[contact])>  
**Subject:** RE: RELIEF Gender Supplemental - revised protocol [version 6.0] ([name] R01AT006978) - UPDATE

[name],

Dynamic trunk stiffness can be determined from the data collected on all participants in Group 2 (Spinal Effects) as the data necessary for these calculations were collected as part of the approved protocol, but this analysis **was not** explicitly proposed in the original DSP. The Co-I on gender supplemental, [name], is the bioengineer who designed the puller apparatus used to deliver the trunk perturbations. He will now assist in developing the software necessary to derive dynamic trunk stiffness from the data already collected.

Please let me know if you need any additional information or clarification on this issue.

Regards,

[name]

UPDATE: Had an error in the first response (“was” should have been “was not”). Sent the first reply too early in the morning.

---

**From:** [name] (NIH/NCCIH) [E] [<mailto:[contact]>]

**Sent:** Wednesday, June 29, 2016 4:57 PM

**To:** [name]

**Subject:** FW: RELIEF Gender Supplemental - revised protocol [version 6.0] ([name] R01AT006978)

Dear [name],

As part of NCCIH’s review of the revised study protocol (including the new supplement), would you please clarify for NCCIH the answer to the following question:

It appears that a new measure (i.e., Dynamic Trunk Stiffness) has been added to the protocol.

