### 1.1 Mechanistic Component

The primary objective of the mechanistic component is to identify the physiological and biomechanical bases for changes in pain and disability associated with the respective interventions. As stated previously, participants will be recruited and enrolled into three separate experiments and then randomly assigned to one of three treatment arms. Additionally, for this objective we seek to determine the 1) acute effects of manual therapies, 2) the effects following a 3-week course of treatment, and 3) the sustained effects assessed approximately 1 month after completing the course of treatment. Thus, for this objective we will include 4 assessment points (baseline plus the 3 time points described above) for our physiological outcome measures. Below we outline the primary physiological outcomes for each group.

- Group 1 (Muscular Effects): Subjects assigned to this group will undergo a magnetic resonance imaging examination to quantify the skeletal muscle proton transverse relaxation time (T2) of the lumbar muscles.
- Group 2 (Spinal Effects): Subjects assigned to this group will undergo neurophysiological and biomechanical examinations to quantify short-latency stretch reflex excitability, trunk muscle onset latencies in response to postural perturbations, and lumbar motion during volitional movement tasks.
- Group 3 (Cortical Effects): Subjects assigned to this experiment will undergo a transcranial magnetic stimulation protocol to quantify motor evoked potential amplitude, intracortical facilitation, and short-interval intracortical inhibition.

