### Assessments (visits 8 & 9)

The following clinical outcomes and evaluation data will be obtained from all study participants between days 23-25 of the study (post-treatment measures) and between days 57-61 of the study (follow-up measures):

- NPR

- RMDQ
- Prior & Concomitant Medication Form
- Change in Medication Use
- Treatment Administration

The following physiological outcomes will be obtained based the experimental group to which they are randomly assigned (i.e., muscular, spinal, cortical) 3-days +/-2-days (post-treatment measures) and 28-days +/-4-days (follow-up measures) following the final study intervention (visit 7):

- Group 1 (Muscular Effects):
  - Skeletal muscle proton transverse relaxation time (T2) of the lumbar muscles.
- Group 2 (Spinal Effects)
  - Short-latency stretch reflex excitability.
  - Trunk muscle onset latencies in response to postural perturbations.
  - Lumbar motion during volitional movement tasks
  - Dynamic trunk stiffness
- Group 3 (Cortical Effects)
  - Motor evoked potential amplitude
  - Intracortical facilitation
  - Short-interval intracortical inhibition

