### **Detailed Analytic Approach:**

Linear mixed-effects regression (LMER) analyses will serve as the main analytic framework, because it offers distinct advantages in statistical power and estimation of population parameters over ANOVA or MANOVA. First, LMER easily incorporates miscellaneous factors (e.g., blocks and treatment providers) as random effects so that the variances due to those factors can be partitioned. As a result, LMER models typically offer less biased parameter estimation and can also offer higher statistical power. It can model multiple dependent variables (e.g., motor evoked potential amplitude, intracortical facilitation, and short-interval intracortical inhibition for Group 3) and test the effect of treatment for each of these dependent variables simultaneously. This modeling technique avoids alpha inflations which typically result from multiple testing. Finally, LMER's maximum-likelihood estimation allows patients with missing observations to be included in a model if the observations are missing completely at random or missing at random. This advantage is important because some degree of attrition is unavoidable given the longitudinal nature of our project. Because we will stratify our samples by sex, sex will be included in each of the models we will describe below. We will test the significant main effect of sex as well as its interaction with the Treatment factor.

- **Intention to Treat Analysis (ITT):** We will include all randomized study participants who have at least baseline endpoint assessments in our ITT analysis. The ITT analysis is our primary method for assessing outcomes, and how it is performed will be determined based on the pattern of

missingness. If the missingness is deemed MCAR, the LOCF method will be used: simply the most recent valid observation will be "carried forward" to replace the subsequent missing observations. If the missingness is deemed MAR, missing observations will remain as missing, and maximum-likelihood estimation, the default estimation algorithm of LMER, will be used to estimate these observations. If the missingness is found to be MNAR, multiple-imputed data will be used to construct LMER models.

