## Exclusion criteria

Participants must not have any of the following exclusion criteria to participate in this study:

- Have a personal history of the following neurological disorders: Alzheimer's, Amyotrophic Lateral Sclerosis, Multiple Sclerosis, Parkinson's, or Stroke.
- Have a personal history of the following cardiorespiratory disorders: Congestive heart failure, Heart attack in past 24 months.
- Have a personal history of the following musculoskeletal disorders: Rheumatoid Arthritis, pathologic fractures of the spine, avascular necrosis or osteonecrosis, severe osteoarthritis. Including a history of spine surgery or a hip arthroplasty.
- Have active cancer.
- Be Blind.
- Have used narcotics or muscle relaxants within 30 days prior to study enrollment.
- Report being pregnant.
- Have a body mass index greater than 35 kg/m^2.
- Have clinical depression (i.e., subjects who score 24 or higher on the Center for Epidemiology Depression Scale).
- Current drug or alcohol use or dependence that, in the opinion of the PIs, would interfere with adherence to study requirements

## Hypothesis Testing: Aim 1

Hypothesis 1.1. Male participants with chronic LBP will present with increased stiffness compared female participants with chronic LBP

Hypothesis 1.2. Participants with chronic LBP will present with increased stiffness compared healthy controls.

Separate 2 Group (Chronic LBP, Matched Healthy Control) x 2 Sex (Male, Female) mixed-model MANOVAs will be conducted on trunk stiffness measures.

## Hypothesis Testing: Aim 2

Hypothesis 2.1. There are no net sex effects of spinal manipulation on trunk stiffness.

Hypothesis 2.2. Both manipulative interventions will decrease passive trunk stiffness as evidenced by the trunk's initial mechanical response to multi-directional trunk perturbations.

Separate 3 Group (Manipulation, Mobilization, Sham Laser) x 2 Gender (Male, Female) x 3 Time (Baseline, Immediately following initial treatment, 48 hrs post-3 weeks of treatment) mixed-model MANOVAs will be conducted on trunk stiffness measures.

**Specific Aim 3.** To examine the effects of sex and posture on trunk stiffness.

**Hypothesis 3.1.** Healthy Male participants will present with increased trunk stiffness compared to healthy female participants.

**Hypothesis 3.2.** Trunk stiffness will be greater in sitting compared to standing.

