### **Experiment 2. Spinal Effects**

- ☐ Instrument study participant for EMG.
- ☐ Instrument study participant for motion capture.
- ☐ Perform The RELIEF Study short latency spinal reflex protocol
- ☐ Perform The RELIEF Study standardized reaching protocol.
- ☐ Perform The RELIEF Study trunk perturbation protocol.
- ☐ If necessary repeat a trial and delete prior file.
- ☐ Save files to lab secure network hard drive and back-up to cloud.

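### Dynamic trunk stiffness is scheduled at the 4-week follow-up (Visit 9, OA4), but no written analysis uses it there, and the Aim 2 model sets no missing-data rule

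*Supplement*

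**What the plan says.** **Measurement.** Dynamic trunk stiffness is listed among the mechanistic outcomes in the Précis, section 3 and section 9.4. Section 6.2.4 schedules it after the first treatment (OA2). Under Assessments (visits 8 & 9) the Group 2 list again includes "Dynamic trunk stiffness", with the last assessment at "28-days +/-4-days (follow-up measures) following the final study intervention (visit 7"). The Experiment 2 checklists for Visit 2 (before and after treatment), Visit 8 and Visit 9 all carry the same task: "Perform The RELIEF Study trunk perturbation protocol". The investigator's reply to NCCIH of June 2016 says "Dynamic trunk stiffness can be determined from the data collected on all participants in Group 2 (Spinal Effects").

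**Objective.** Section 1.1 states: "we will include 4 assessment points (baseline plus the 3 time points described above) for our physiological outcome measures". The third of those time points is "the sustained effects assessed approximately 1 month after completing the course of treatment".

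**Analysis.** Section 9.5 specifies tests at OA2, OA3 and OA4 for stretch reflex, onset latencies and lumbar motion. It does not name stiffness, and it places the supplement's data analysis in the appendix. In the appendix, Hypothesis Testing: Aim 2 crosses treatment group and sex with "3 Time (Baseline, Immediately following initial treatment, 48 hrs post-3 weeks of treatment) mixed-model MANOVAs will be conducted on trunk stiffness measures". No rule for missing data is given there. Section 9.5 chooses LMER for the mechanistic and RCT data because "it offers distinct advantages in statistical power and estimation of population parameters over ANOVA or MANOVA", and adds that it lets participants with missing observations stay in the model.

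**The concern.** Two gaps meet in one paragraph of the appendix.

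First, a listed outcome is collected at OA4 and no analysis of it there is written down, although the parent protocol asks about sustained effects on physiological outcomes. At stake is whether any treatment effect on stiffness lasts, and also pre-specification. The appendix reports 18 men and 31 women, 49 of 60, already tested in Experiment 2 when the supplement was written, and stiffness is derived from recordings already made. Without a rule, OA4 stiffness could be reported or left out after the results are known.

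Second, the treatment analysis of stiffness moves from the plan's preferred model to a MANOVA and does not say what happens to a participant with a missing visit or an unusable record. A classical repeated-measures MANOVA usually deletes such participants. That costs power, and it can bias the comparison if dropout is related to response.

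**Working it through.** The documents give no sample size derivation, power or alpha for Aim 2 beyond saying that 60 participants should suffice, so there is no stated figure to reproduce. The check is a cross-reading and a count.

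**Cross-reading, low back pain participants in Experiment 2**

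| Assessment | Stiffness data scheduled | Written stiffness analysis |
|---|---|---|
| OA1 (Visit 2, before treatment) | Yes, perturbation task in the Visit 2 checklist | Yes, Aims 1 and 2 |
| OA2 (Visit 2, after treatment) | Yes, section 6.2.4 | Yes, Aim 2 |
| OA3 (Visit 8) | Yes, section 6.2.4 | Yes, Aim 2, labelled as 48 hours |
| OA4 (Visit 9) | Yes, section 6.2.4 and Visit 9 checklist | None in section 9.5 or the appendix |

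**Share of assessments with no planned use**

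Inputs: 60 low back pain participants in Experiment 2; 4 assessments (section 1.1); 10% attrition at OA3 or OA4 (section 9.2 simulation assumptions); 60 healthy controls tested once, seated and then standing (appendix).

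- Full attendance: 60 × 4 = 240 planned; OA4 = 60; 60/240 = 25.0%.
- Attrition of 0.10 × 60 = 6, all at OA4: 60 + 60 + 60 + 54 = 234; 54/234 = 23.1%.
- Attrition of 6, all at OA3: 60 + 60 + 54 + 54 = 228; 54/228 = 23.7%.
- Counting the controls' seated test (full attendance): 60/(240 + 60) = 20.0%.
- Counting their seated and standing tests: 60/(240 + 120) = 16.7%.

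**Missing data**

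The only planning figure is the 10% attrition. If participants with a missing visit were deleted, a three-visit analysis would keep 54 to 60 of 60, depending on when the dropouts occur, and a four-visit analysis would keep 54. A likelihood-based mixed model could use the available records of all 60. This is conditional arithmetic, not an estimate. The documents give no rate of unusable recordings. They also do not say whether the three planes enter one MANOVA or separate ones, so the loss from that source cannot be computed.

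**The 48-hour label**

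Visit 8 is 3 days ± 1 day after the last treatment in sections 3 and 9.1, and ± 2 days for the physiological measures in section 6.2.4. Forty-eight hours lies inside both windows, so the label is out of date but the visit meant is clear.

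**The case against.** The strongest reply is that Aim 2 does what it sets out to do. The Précis and the appendix both frame the supplement's question as change after the first treatment and after the 3-week course, and hypotheses 2.1 and 2.2 claim nothing about persistence. Three time levels answer that question. This stands: the appendix is consistent with itself, and the gap lies between it and the parent protocol.

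A second reply is that the sustained-effects objective belongs to the parent study, and the Group 2 paragraph of section 1.1 does not name stiffness. If stiffness is instead a parent outcome, the general LMER framework of section 9.5 already covers it and only a line is missing. This has some force. But the Précis and sections 3, 6.2.4 and 9.4 do treat stiffness as a Group 2 outcome, section 9.5 refers the supplement's analysis to the appendix, and the appendix names a different model. Neither reading yields a written OA4 test.

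Some stronger readings are tempting, and the documents do not support them:

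- *A reader might infer that Aim 2 is a complete-case analysis.* The text says only mixed-model MANOVA. Deletion is the usual behaviour of the classical method, not a stated rule.
- *A reader might put a figure on the participants lost by multiplying assumed failure rates over planes and visits.* No such rate is given, several loads are applied per direction, and the checklists allow trials to be repeated.
- *A reader might say a quarter of all stiffness data goes unused.* That share holds only for the low back pain participants' planned assessments.
- *A reader might conclude that the persistence question, or even recurrence of back pain, can no longer be addressed.* The OA4 recordings are kept, nothing forbids a later analysis, and no recurrence endpoint exists.

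**Conclusion.** The point holds as a gap in specification. Stiffness at OA4 is scheduled, falls under a four-assessment design with a sustained-effects objective, and has no written analysis. The size is up to 60 of 240 planned assessments in the low back pain participants (25%), about 23-24% under the plan's 10% attrition, and 17-20% if controls are counted at full attendance. These counts rest on the planned enrolment of 60 and on each participant contributing one assessment per scheduled time.

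The choice of MANOVA without a missing-data rule departs from the preference stated in section 9.5 and leaves open a risk of deleting incomplete participants. It is not evidence that deletion is planned. The RCT co-primary outcomes and the powered mechanistic hypotheses are unaffected. A better method already stands in the plan and the data are already scheduled, so the change is worth making.

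**What to change.** In the appendix, under Hypothesis Testing: Aim 2:

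- Replace the MANOVA with the section 9.5 LMER over OA2, OA3 and OA4, with baseline stiffness as covariate and treatment, sex and their interaction with each other and with time, using all available records.
- Pre-specify contrasts of each manual therapy against sham at each assessment. Keep OA2 and OA3 as the Aim 2 tests and label OA4 as the secondary, sustained-effect contrast.
- State the missing-data rule, and say whether planes are modelled jointly or separately.
- Replace the 48-hour label with OA3 (Visit 8).
- Add one line to section 9.5 naming stiffness and pointing to this analysis.

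If the investigators do not want an OA4 test, the minimum is a sentence saying that Visit 9 stiffness is exploratory or will not be analysed, together with the missing-data rule.

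The cost is appendix wording and one changed model, with no new data and one more time point in any multiplicity count.

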## Timeline

| Tasks       | Q1                                                                        | Q2                                                                                           | Q3            | Q4                    |
|-------------|---------------------------------------------------------------------------|----------------------------------------------------------------------------------------------|---------------|-----------------------|
| Aims 1, 3,4 | Develop stiffness models

Begin recruiting matched healthy controls | Enroll & test matched healthy controls

Complete testing for Experiment 2 RELIEF study | Data analyses | Manuscript generation |
| Aim 2       | Complete testing for Experiment 2 RELIEF study                            |                                                                                              | Data analyses | Manuscript generation |

## Summary

The research represents a critical assessment of sex differences in trunk stiffness assessed in the three cardinal planes. Our low-mass system allows us to assess dynamic trunk stiffness with great sensitivity and this will be the first study to examine sex differences in dynamic stiffness in a cohort of chronic LBP sufferers who meet a clinical prediction for spinal manipulation (i.e., have a clinician identified hypo-mobile segment). We are uniquely positioned to provide the first and most comprehensive study of sex differences in a known factor in recurrent and chronic LBP. This research has a strong potential to positively impact public health by providing data required to develop innovative, individualized treatments to prevent recurrent low back pain and related disability.

# SOP: Protocol Deviations

---

## **OBJECTIVE**

To describe the policies and procedures for defining, identifying, attributing, dating, signing, and reporting Protocol Deviations.

## **GENERAL DESCRIPTION**

- a. Protocol Deviation is defined
- b. Protocol Deviation is identified
- c. Protocol Deviation is assigned attributions
- d. Protocol Deviation is dated
- e. Protocol Deviation is signed
- f. Protocol Deviation is reported

## **DEFINITIONS**

Protocol Deviation (PD): A variance in a research study between the protocol that has been reviewed and approved by the IRB and the actual performance within the research study, with no substantive effect on the risks to research participants, no substantive effect on the value of the data collected (i.e., the variance does not confound the scientific analysis of the results), and did not result from willful or knowing misconduct on the part of the investigators. (IRB Policy/Procedures Guidelines for the Compliance Office, Revision date 1 July 2016, Section 23.0, Pages 44-45)

Minor Protocol Deviation: a change, divergence, or departure from the study design or procedures that does not affect the scientific soundness of the research plan or the rights, safety, or welfare of human subjects. (Ref: Email from [name], Director of Compliance, dated 17 May 2016 at 9:49 AM)

## **RESPONSIBILITY**

Execution of SOP: Principal Investigator (PI), Co-Investigators, Study Coordinator, Research Assistants, Study Personnel, Independent Monitoring Committee, Sponsor (National Institutes of Health) Program Officer, IRB Chair, IRB, Office of Research Compliance (ORC), ORC Staff

## **PROCEDURES**

[figure not shown]

**OHIO**  
UNIVERSITY

[figure not shown]

OHIO MUSCULOSKELETAL  
AND NEUROLOGICAL INSTITUTE  
Heritage College of Osteopathic Medicine

The RELIEF Study  
Standard Operating Procedure  
16 November 2016

[figure not shown]

- a. Protocol Deviation is defined according to IRB Policies & Procedures, the Detailed Study Protocol, Independent Monitoring Committee Data & Safety Monitoring Plan, CFR, ICH, and GCP standards
  - 1) Definition: A variance in a research study between the protocol that has been reviewed and approved by the IRB and the actual performance within the research study, with no substantive effect on the risks to research participants, no substantive effect on the value of the data collected (i.e., the variance does not confound the scientific analysis of the results), and did not result from willful or knowing misconduct on the part of the investigators. (IRB Policy/Procedures Guidelines for the Compliance Office, Revision date 1 July 2016, Section 23.0, Pages 44-45)
    - i. Exemption: A minor protocol deviation is defined as a change, divergence, or departure from the study design or procedures that does not affect the scientific soundness of the research plan or the rights, safety, or welfare of human subjects. Examples of minor or administrative deviations include missed visits, assessments/visits/procedures occurring outside of protocol “windows” or timelines due to scheduling issues or natural events (e.g., weather, University emergency closure), and minor documentation errors (e.g., incorrect date format). (Ref: Email from [name], Director of Compliance, dated 17 May 2016 at 9:49 AM)
- b. Protocol Deviation is identified by study staff and documented in the Case Report Form in the Protocol Deviation Form noting description, category & code, date and time of occurrence.
- c. Protocol Deviation is assigned attributions by the Study Coordinator under the direct guidance of the Principal Investigator using the following Deviation Category & Code:

CATEGORY A: SAFETY

1. Not reporting an SAE within 24 hours
2. Laboratory tests not done
3. AE/SAE is not reported to IRB
4. Other

CATEGORY B: INFORMED CONSENT

6. Failure to obtain informed consent
7. Consent Form used was not current IRB approved version
8. Consent form does not include updates or information required by IRB
9. Consent form missing
10. Consent form not signed and dated by participant
11. Consent form does not contain all required signatures
12. Other

CATEGORY C: ELIGIBILITY

1. Participant did not meet eligibility criterion
2. Randomization of an ineligible participant
3. Participant randomized prior to completing baseline assessment, etc.

[figure not shown]

